## Abstract

**Background:**

Electroconvulsive therapy (ECT) is a highly effective treatment for depressive disorder. However, the use of ECT is limited by its cognitive side effects (CSEs), and no specific intervention has been developed to address this problem. As transcranial direct current stimulation (tDCS) is a safe and useful tool for improving cognitive function, the main objective of this study was to explore the ability to use tDCS after ECT to ameliorate the cognitive side effects.

**Methods:**

60 eligible participants will be recruited within two days after completing ECT course and randomly assigned to receive either active or sham stimulation in a blinded, parallel-design trial and continue their usual pharmacotherapy. The tDCS protocol consists of 30-min sessions at 2 mA, 5 times per week for 2 consecutive weeks, applied through 15-cm^2^ electrodes. An anode will be placed over the left dorsolateral prefrontal cortex (DLPFC), and a cathode will be placed over the right supraorbital cortex. Cognitive function and depressive symptoms will be assessed before the first stimulation (T0), after the final stimulation (T1), 2 weeks after the final stimulation (T2), and 4 weeks after the final stimulation (T3) using the Cambridge Neuropsychological Test Automated Battery (CANTAB).

**Discussion:**

We describe a novel clinical trial to explore whether the administration of tDCS after completing ECT course can accelerates recovery from the CSEs. We hypothesized that the active group would recover faster from the CSEs and be superior to the sham group. If our hypothesis is supported, the use of tDCS could benefit eligible patients who are reluctant to receive ECT and reduce the risk of self-inflicted or suicide due to delays in treatment.

**Trial registration details:**

The trial protocol is registered with https://www.chictr.org.cn/ under protocol registration number ChiCTR2300071147 (date of registration: 05.06.2023). Recruitment will start in November 2023.

**Supplementary Information:**

The online version contains supplementary material available at 10.1186/s12888-024-05567-9.

## Introduction

### Background

Electroconvulsive therapy (ECT) stands out as an effective and rapid treatment for major depressive disorder (MDD) patients [1]. However, concerns about potential cognitive side effects (CSEs) deter patients from consenting to ECT [2]. While most deficits, including memory, executive function, attention, and processing speed, are transient [3, 4], sensitive assessment tools suggest that spatial recognition memory impairment can persist for more than a month following ECT [5, 6]. Furthermore, patients reported a deleterious effect on memory persisting 24 weeks post-ECT using Global Self-Evaluation—Memory [7, 8].

The underlying cause of cognitive impairment following ECT remains unclear. Hippocampal enlargement after ECT is posited to have a significant correlation with cognitive dysfunction [9–12], potentially attributable to the interference of neuroplastic alterations with existing synaptic connections following ECT [9, 10]. Besides, a consistently replicated finding points to reduced prefrontal cerebral blood flow (CBF) and metabolism post-ECT [13–16]. Moreover, challenging conventional perspectives, the question arises: are the antidepressant effects and the CSEs of ECT a consequence of the seizure, the electrical stimulation, or a combination of both [17–19]?

To mitigate CSEs, researchers have pursued various approaches. Significantly, advancements in electrode placement and electrical parameters, such as high dosage right unilateral ECT and ultra-brief pulse width ECT, have effectively reduced CSEs [20–22]. However, some studies indicate that compared to right unilateral ECT, bilateral ECT demonstrates higher efficacy and may offer a quicker onset of action [23–25]. Similarly, brief pulse width right unilateral ECT showed slightly higher effectiveness in treating depression with fewer sessions than ultra-brief pulse width right unilateral ECT [20]. In addition, extensive research has been dedicated to pharmacological interventions [26]. Notably, although promising medications like liothyronine [27], memantine [28, 29], and galantamine [30] have been reported to potentially alleviate CSEs, further rigorous trials are indispensable to verify their appropriateness for routine clinical application. In sum, exploring alternative strategies becomes imperative.

Transcranial direct current stimulation (tDCS) is a non-invasive, effective, and affordable brain stimulation tool with mild side effects [31, 32]. Consequently, tDCS has been widely applied in the field of neuropsychiatry to enhancing cognitive function. Studies have demonstrated that tDCS applied to frontal and temporal regions, with the most commonly stimulated site being the dorsolateral prefrontal cortex (DLPFC), can modulate specific neural circuits, thereby elicit a transdiagnostic enhancement of working memory and attention [33]. This effect has been observed in various conditions, including Depressive Disorder [34], Schizophrenia [35], Bipolar Disorder [36], Attention-Deficit/Hyperactivity Disorder [37], Alzheimer's disease [38] and Parkinson's disease [39]. Furthermore, some articles have revealed that anodal tDCS over the DLPFC can decrease response time [40, 41], improves executive function [42], boosts episodic memories [43, 44] and promotes other cognitive performance [45] in healthy participants. Additionally, the increased CBF [46–48] and cortical activity [49–51] induced by anodal stimulation are likely to improve the ECT-induced reduction in frontal CBF and metabolism [13, 14, 16]. However, such research remains largely unexplored to date. Therefore, utilization tDCS to ameliorate CSEs in ECT appears promising and merits further investigation.

## Method

### Objective

The primary objective of this study is to determine whether the implementation of active tDCS after completing the ECT course accelerates recovery from the CSEs, especially the spatial recognition memory.

Secondary, the study aims at examining the long-term (after 4 weeks) effects in improving cognitive function and the whether the implementation of tDCS after the ECT course decrease the relapse of depressive symptoms.

### Study design and setting

This is a randomized, double-blind, sham-controlled, interventional trial. 60 eligible participants will be recruited within two days after the last ECT session and randomly allocated into two groups in a 1:1 ratio: active tDCS (intervention group) and sham tDCS (control group). Assessments will be conducted at the following time points: before the first tDCS session (T0), immediately after the last tDCS session (T1), 2 weeks post-tDCS (T2), and 4 weeks post-tDCS (T3), using the Cambridge Neuropsychological Test Automated Battery (CANTAB). Table 2 shows schedule of enrolment, intervention, and assessments. Throughout the study, there was no interference or restriction for the patient ‘s physician in charge to adjust psychiatric medications according to the patient’ s condition. Figure 1 represents the research procedure schematically.

**Fig. 1 Fig1:**
[figure not shown]
Flowchart of the study design

This study, approved by the Research Ethics Committee of the First Affiliated Hospital of Chongqing Medical University (Approval Number: 2023–203) and registered with the China Clinical Trials Center (Registration Number: ChiCTR2300071147), will be conducted at one of Southwest China's largest hospitals, the First Affiliated Hospital of Chongqing Medical University, where approximately 40 to 60 patients receive ECT daily. The study design is in accordance with the 2013 Standard Protocol Items: Recommendations for Interventional Trials (SPIRIT) statement [52].

### Recruitment

Participants will be recruited from the Psychiatry Department by the researchers. The study will be advertised on the hospital's website, and we will distribute leaflets to the patients two days prior to their discharge. Prior to screening, all potential participants will receive verbal and written explanations about the study's procedures and potential benefits or risks. Every participant will voluntarily sign the informed consent form (Supplementary Material: informed consent) and can withdraw from the trial at any time. Written informed consent will be obtained from all participants and their legal guardians before their formal inclusion in the study. Compliance will be improved by using WeChat (a popular social communication app in China) for appointment reminders and offering transportation cost reimbursements to reduce dropout among financially constrained participants.

### Participants

Participants will be assessed based on inclusion and exclusion criteria highlighted in Table 1. Throughout the study, researchers may opt to discontinue a participant's involvement due to urgent medical circumstances or if the participant's condition changes to the extent that they no longer meet the eligibility criteria for participation.

**Table 1 Tab1:** Inclusion and exclusion criteria

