**Inclusion criteria:**
1. Aged 18 to 65 years
2. Right-handed
3. Diagnosed with MDD based on DSM-5 criteria by at least one qualified psychiatrist
4. 24-item Hamilton Rating Scale for Depression (HAMD-24) score ≥ 17
5. Completed ECT treatment
6. Capable of comprehending and completing the study assessments
7. Written informed consent provided by patients and/or their legal guardians

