### Blinding and unblinding

The tDCS treatment device consists of two parts: a computer and a small stimulator. To prevent participants from being directly aware of their group assignment, the treatment is carried out in a dedicated room, where the patient will sit on a couch positioned away from the computer and the stimulator will be placed in an opaque bag behind the patient. The psychiatrist administering tDCS knows the group assignments but cannot share this with participants or engage in the study’s evaluation or analysis. Additionally, the assessors and data analysts will be kept unaware of the intervention groups. To evaluate the adequacy of blinding procedures, participants will be invited to make an educated guess regarding their treatment assignment after the tDCS sessions.

If there is a suspicion of a severe adverse reaction or if clinical psychiatrists determine it is essential for participant safety, disclosure of group membership may be required.

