### Intervention

tDCS will be administered using a battery-driven direct current stimulator (EM8010S, Yimai Medical Technology Co., Ltd. Wuhan, China) via a pair of identical squares (3 × 5 cm) saline-soaked sponge electrodes secured in place with elastic bands. The anodal electrodes will be positioned over the F3 site, corresponding to the DLPFC following the EEG10– 20 international system. Conversely, the cathodal electrode will be placed above the Fp2 site, corresponding to the right supraorbital region. Within two days after completing the ECT course, all study participants will receive tDCS five times per week, once daily, for two consecutive weeks. In the active tDCS condition, each session will deliver a direct current of 2 mA for 30 min. In the sham tDCS condition, stimulation will be administered using the same active tDCS montage. The stimulation intensity will be set at 2 mA, but the current will be applied for 1 min with a 30-s ramp-up and ramp-down. In prior studies [53], this approach ensured participant blinding regarding the stimulation type (active vs. sham).

During the intervention, participants will continue their usual pharmacotherapy, but transcranial magnetic stimulation or other neuromodulation treatments are forbidden. The intervention will be discontinued if there are any severe adverse effects or withdrawal. This trial is deemed of minimal risk to study participants. Therefore, there are no provisions for ancillary or posttrial care.

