### Outcome

To assess cognitive changes, we will employ the CANTAB, a tool previously demonstrated to be highly sensitive in evaluating the cognitive side effects of ECT [5, 6]. Additionally, we have chosen a set of five tests designed to assess frontal lobe function. To mitigate potential learning effects, different parallel versions of the same test will be employed during various assessment phases. Assessments of cognitive function and depressive symptoms will be conducted before the first tDCS session (T0), immediately after the last tDCS session (T1), 2 weeks post-tDCS (T2), and 4 weeks post-tDCS (T3). The detailed visit procedure is shown in Table 2.

**Table 2 Tab2:** Schedule of enrolment, intervention, and assessments

	Enrolment	Baseline	Intervention	Follow-up	
		Before tDCS	After tDCS	after 2 weeks	After 4 weeks
Time point		T0	T1	T2	T3
Enrolment					
Eligibility screening	√				
Informed consent	√				
Allocation	√				
Demographic data		√			
Intervention					
Active tDCS			√		
Sham tDCS			√		
Assessments					
CANTAB					
SRM		√	√	√	√
SWM		√	√	√	√
RVP		√	√	√	√
VRM		√	√	√	√
SOC		√	√	√	√
HAMD-24		√	√	√	√
SDS		√	√	√	√
tDCS-AEQ^a^			√		
Blinding			√		

*a: test after every tDCS session*

*CANTAB: Cambridge Neuropsychological Test Automated Battery, HAMD-24: Hamilton depression rating scale; RVP: Rapid visual information processing; SDS: Self-rating depression scale; SOC: Stockings of Cambridge; SRM: Spatial recognition memory; SWM: Spatial working memory; VRM: Verbal Recognition Memory; tDCS, transcranial direct current stimulation; tDCS-AEQ: Transcranial direct current stimulation adverse effects questionnaire*

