### Second outcome

Spatial Working Memory (SWM) assesses the subject's ability to retain and manipulate spatial information in working memory. The outcome measures include between errors, within errors, and strategy employed. A high strategy score represents poor use of strategy, and a low score equates to effective use.Verbal Recognition Memory (VRM) evaluates immediate and delayed verbal information memory. Outcome measures include the total number of correct words in the free recall phase, the total of all correctly identified words in the immediate recognition phase, and the delayed recognition phase.Rapid Visual Information Processing (RVP) assesses visual sustained attention. Outcome measures include mean latency and total correct responses.Stockings of Cambridge (SOC) evaluates spatial planning and spatial working memory. Outcome measures include the number of n-move problems solved in the minimum moves, mean moves for n-move problems, mean initial thinking time for n-move problems, and mean subsequent thinking time for n-move problems.Assessing the degree of depressive symptom with the Hamilton Depression Rating Scale (HAMD-24) [56] and the Self-rated Depression Scale (SDS) [57, 58].

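### The discontinuation rule re-applies the entry criteria after randomisation, without saying which are entry-only, and so permits outcome-related loss of follow-up, mainly at T2 and T3

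*Protocol article*

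**What the plan says.** - **Participants.** The rule begins "Throughout the study, researchers may opt to discontinue" a participant's involvement. The grounds are urgent medical circumstances, or that the participant's "condition changes to the extent that they no longer meet the eligibility criteria for participation". The criteria meant are those of Table 1.
- **Table 1, inclusion 4.** "24-item Hamilton Rating Scale for Depression (HAMD-24) score ≥ 17", with no time point: before ECT, at enrolment after ECT, or continuing. Inclusion 6 requires that the person can understand and complete the assessments. Exclusion 6 is ECT within the past six months.
- **Outcome and Table 2.** "Assessments of cognitive function and depressive symptoms will be conducted before the first tDCS session (T0"), and again at T1, T2 and T3. SRM and HAMD-24 share these four visits.
- **Second outcome.** HAMD-24 is listed as an outcome: "Assessing the degree of depressive symptom with the Hamilton Depression Rating Scale (HAMD-24").
- **Objective.** A secondary aim is to learn whether "tDCS after the ECT course decrease the relapse of depressive symptoms".
- **Intervention.** Stopping stimulation has a rule of its own: "The intervention will be discontinued if there are any severe adverse effects or withdrawal".
- **Sample size.** 24 per group are needed, raised to 30 for 20% dropout.

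**The concern.** Eligibility describes a person at entry. Here it is re-applied after randomisation, at the researchers' discretion, and it can end involvement in the study. Because stimulation has a separate stopping rule with different grounds, the wording under Participants reads as covering assessments as well as sessions.

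One of the criteria is an outcome of the trial. A participant whose HAMD-24 falls below 17 no longer meets inclusion 4 as written and may be discontinued. If tDCS affects mood, the number open to removal can differ between the arms. Relapse is the clearest casualty: the people in whom a relapse can be seen are those who have first improved, and they are the ones this reading would allow to leave before T2 and T3. Inclusion 6 opens a second route, through cognition, for those who deteriorate.

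**Working it through.** **1. Can the rule work as written?** Every participant has just completed ECT (inclusion 5; recruitment is within two days of the last session). If exclusion 6 were a continuing condition, all participants would fail it from the start. So at least one criterion must be entry-only, and the text does not say which others are.

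**2. Which assessments are exposed?** T0 precedes stimulation, so a score below 17 there is not a treatment effect. The next scheduled HAMD-24 is at T1, the visit at which SRM is also due. A scheduled score below 17 therefore threatens T2 and T3 and largely spares the immediate post-treatment SRM comparison.

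**3. The plan's margin.** 24 / (1 − 0.20) = 30, as stated, so 30 − 24 = 6 losses per group are allowed for, from all causes. The article quotes 37.5% dropout in the prior study; at that rate 30 × 0.625 = 18.75 would remain before any discretionary removal.

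Falling below 24 is a shortfall against the plan's own requirement, not automatically a loss of 80% power. With δ = 16.20 and σ = 15.03, n = 2(1.960 + 0.842)² × 15.03² / 16.20² = 13.5, i.e. 14 per group (15 by t-test). The 24 is reached from 15 / 0.625, or approximately (23 by t-test) with δ = 0.20 × 64.67 = 12.93. Two-sided t-test power:

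| n per group | δ = 16.20 | δ = 12.93 |
|---|---|---|
| 24 | 95% | 83% |
| 20 | 91% | 76% |
| 15 | 81% | 62% |

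**4. Bias among those retained.** Let p be the proportion removed in an arm and D the mean SRM of removed minus retained participants. Then retained mean = overall mean − p × D. With the same D in both arms, the retained difference is shifted by −(p_active − p_sham) × D. It is zero if removal is equal in the arms or if removed and retained do not differ in SRM. The documents give neither p nor D.

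**5. Illustration, on assumed values that are not in the documents.** T0 HAMD-24 is normal (mean 20, SD 5) cut off below 17. By T1 it falls by 3 on average (SD 5), plus an extra fall in the active arm. T3 equals T1 plus noise of SD 4. Everyone below 17 at T1 is removed. SRM has SD 15.03, a true difference of about 12.9, and correlation ρ with T1 HAMD-24.

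| Extra fall, active | Removed, sham / active | T3 HAMD-24 difference, all / retained | SRM difference retained, ρ = 0 | ρ = −0.3 | ρ = −0.5 |
|---|---|---|---|---|---|
| 0 | 36% / 36% | 0 / 0 | 12.8 | 12.9 | 12.9 |
| 2 | 36% / 49% | −2.0 / −0.8 | 13.0 | 12.0 | 11.4 |
| 4 | 36% / 62% | −4.0 / −1.4 | 13.0 | 11.1 | 9.7 |

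Simulation error in the SRM columns is about 0.1. The illustration removes everyone who qualifies, whereas the rule is discretionary. It also compares raw means of those retained, whereas the plan uses mixed models. It shows direction and conditions, not an expected size.

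**The case against.** The best defence is that nobody meant to remove patients for getting better. The clause stands beside urgent medical circumstances and naturally covers new disqualifying events such as pregnancy, a seizure disorder or a changed diagnosis. Removing improvers would defeat the relapse objective and the HAMD-24 schedule, and the absurd result for exclusion 6 suggests that entry-only criteria were taken for granted. This is a fair account of the probable intent. It does not change what the text permits, and a rule that has to be read selectively should say how.

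Several stronger readings are tempting and should be resisted:

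- **That improved patients must be removed.** The rule says researchers may; it does not oblige them.
- **That removed patients are excluded from analysis, so the comparison covers only those who stayed ill.** Ending involvement is not deleting data. Statistical methods plans mixed regression models, which can keep earlier visits. Where removal depends on recorded scores, such a model can reduce the bias. It cannot restore visits never made, and HAMD-24 enters as a covariate only through stepwise selection. The article's silence on an analysis set is no fault, since that commonly stands in a fuller document.
- **That the primary SRM effect is biased by a known amount.** For instance, 40% against 20% removed and a 10-point SRM gap would give (0.40 − 0.20) × 10 = 2.0 points, but none of these inputs has a source. Removal of those who deteriorate, through inclusion 6, raises the retained mean instead of lowering it, so the net effect has no determined sign.
- **That unblinded staff make the decision.** Blinding and unblinding states that "The psychiatrist administering tDCS knows the group assignments" and bars that person from evaluation and analysis. Nothing says that this person decides on discontinuation.

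**Conclusion.** The point holds as a defect of wording with statistical consequences. The rule under Participants, read with Table 1, permits discretionary and outcome-related loss of assessments after randomisation, mainly at T2 and T3.

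The harm to HAMD-24 and relapse is direct, because the possible trigger is the outcome itself. Bias in later SRM comparisons requires that tDCS affects mood and that mood and SRM are related; without either, the HAMD-24 route does not bias SRM. The size cannot be derived from the documents. What they do fix is the margin: more than 6 losses of 30 in a group, from all causes together, leaves fewer than the 24 stated as needed.

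The documents do not show that such removals are intended, that they would be frequent, or that removed participants would be left out of the analysis. The change is worth making because it is specific and cheap.

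**What to change.** 1. Under Participants, state that the Table 1 criteria, including HAMD-24 of at least 17, are assessed at entry, and that no longer meeting them is not in itself a ground for ending follow-up. Give the time point to which the HAMD-24 criterion refers.
2. Reconcile this rule with the stopping rule under Intervention, so that the text separates stopping stimulation from leaving the study. The clinical grounds for stopping stimulation stay with the sponsor.
3. State that participants who stop stimulation continue the scheduled T1 to T3 assessments unless they withdraw consent.

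This needs no new analysis-set rule in the article and leaves the sponsor's safety grounds untouched. The cost is an amendment of wording and some follow-up visits, already in Table 2, for participants who would otherwise have been discontinued.

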**Inclusion criteria:**
1. Aged 18 to 65 years
2. Right-handed
3. Diagnosed with MDD based on DSM-5 criteria by at least one qualified psychiatrist
4. 24-item Hamilton Rating Scale for Depression (HAMD-24) score ≥ 17
5. Completed ECT treatment
6. Capable of comprehending and completing the study assessments
7. Written informed consent provided by patients and/or their legal guardians
